## Abstract

**Background:**

Fibromyalgia is characterized by chronic generalized pain, fatigue, sleep disorders and other symptoms. Physical exercise is recommended as the first choice of non-pharmacological therapy. Thus, the aim of this study is to evaluate the effectiveness and cost-effectiveness of modified Pilates exercises compared to aerobic exercises in the treatment of patients with fibromyalgia.

**Methods:**

In this randomized controlled trial with blinded assessor, 98 patients who meet the fibromyalgia classification criteria of the American College of Rheumatology 2010, aged between 20 and 75 years, and with pain intensity greater than or equal to 3 points in the Pain Numerical Rating Scale, will be randomly divided into Aerobic Group (aerobic exercises on treadmills or stationary bikes) and Pilates Group (modified Pilates exercises), and treated twice a week for eight weeks on the Center for Excellence in Clinical Research in Physical Therapy at Universidade Cidade de São Paulo, Brazil. The following outcomes will be evaluated by a blinded assessor at baseline, eight weeks, six months, and 12 months after randomization: impact of fibromyalgia assessed by the Fibromyalgia Impact Questionnaire, pain intensity by the Pain Numerical Rating Scale, kinesiophobia by the Tampa Scale of Kinesiophobia, specific disability by the Patient-Specific Functional Scale, functional capacity by the 6-min Walk Test, quality of sleep by the Pittsburgh Sleep Quality Index, and health-related quality of life by EQ-5D-3L and SF-6D questionnaires.

**Discussion:**

It is expected that the Pilates exercises will be more effective than aerobic exercises in improving clinical outcomes and that this improvement will be maintained over the medium to long term. This study aims to clarify whether the Pilates method can be incorporated into the clinical practice of physical therapists treating patients with fibromyalgia. The study will also provide information on which exercise will be most cost-effective, information that can be used by insurers and public health systems.

**Trial registration:**

This study was prospectively registered at the Clinical Trials Registry (NCT03050606) in February 2017.

**Electronic supplementary material:**

The online version of this article (10.1186/s41927-018-0051-6) contains supplementary material, which is available to authorized users.

## Background

Fibromyalgia is a rheumatologic disease characterized by chronic generalized pain, hyperalgesia, and allodynia [1]. It is also characterized by the presence of symptoms such as fatigue, sleep disorders, morning stiffness, headache, and paresthesia [1]. It can be classified clinically, following the diagnostic criteria of the American College of Rheumatology 2010 [2]: 1) Widespread Pain Index (WPI), calculated by adding up the number of areas in which the patient reported pain in the last week; and 2) Severity of Symptoms (SS), calculated by adding up the severity of fatigue, waking unrefreshed, cognitive symptoms and somatic symptoms [2]. To be classified as having fibromyalgia, a patient must present the following three clinical conditions: WPI ≥ 7 and SS ≥ 5 or WPI between 3 and 6 and SS ≥ 9 points; presence of symptoms at the same intensity for at least three months; and no disease/condition that could be the cause of the pain [2]. One of the main pathophysiological mechanisms of fibromyalgia is central sensitization, defined as increased responsiveness of nociceptive neurons in the central nervous system to their normal or subthreshold afferent input [3]. In this case, pain can arise spontaneously or be elicited by a normally innocuous stimuli (allodynia), is exaggerated and prolonged in response to a noxious stimuli (hyperalgesia), and spreads beyond the site of injury (secondary hyperalgesia) [4].

The average global prevalence of fibromyalgia is 2.7%, with a higher incidence in women (3:1) [5, 6]. In Brazil, this prevalence is 4.4% in the population aged 35–60 years [7] and 5.5% in people over 65 years of age [8]. Economic impact studies show that patients with fibromyalgia are significant consumers of health services and generate significant costs related to loss of productivity [9]. The average annual cost of fibromyalgia is estimated at approximately 6000 Canadian dollars [10], approximately 2,827,000 Yen of indirect cost and 1,943,000 Yen of direct cost in Japan [11], and this cost is even higher in European patients, approximately 8000 to 13,000 Euros per year [12, 13].

The current recommendation for the treatment of fibromyalgia includes non-pharmacological and self-management strategies combined with pharmacological therapies [14]. Exercise is the first choice of treatment, with stronger evidence for supervised aerobic exercise. However, there is also evidence recommending muscle strengthening and stretching exercises [5, 14, 15]. Some studies [15–17] demonstrate that aerobic exercise improves fibromyalgia symptoms when compared to control groups or other interventions (such as education and cognitive-behavioral therapy). However, the size of these effects is small to moderate [16, 17]. Another type of exercise that can be a good option for the treatment of these patients is the modified Pilates method, as it has exercises to mobilize, stretch, and strengthen muscles. The modified Pilates is currently the most widely used approach by physical therapists, is tailored to the practitioner, divided into levels of progression, and emphasizes the normal curvatures of the spine during the exercises [18]. Pilates exercises are often indicated for the treatment of low back pain [19, 20], but there are only four pilot studies on the effects of the Pilates method in patients with fibromyalgia [21–24]. These studies demonstrate that Pilates may be better than short-term exercise at home [21] and connective tissue massage for pain-pressure threshold and anxiety [22], but similar to yoga exercises [24] and a control group without intervention [23] in patients with fibromyalgia.

A systematic review [25] showed that there is substantial evidence that various modalities of exercise improve pain and function in patients with fibromyalgia but also detected inconclusive evidence for new modalities such as Pilates, yoga and tai chi because of the lack of studies and methodological flaws of the existing studies. This demonstrates the need for studies with adequate comparator groups and samples to verify the actual effectiveness of modified Pilates exercises in this disease. In addition, fibromyalgia generates high costs in health, but there is little information about the cost-effectiveness of the treatments indicated for its control, and it is extremely important to identify the most effective and less costly treatments. Thus, the aim of this study is to evaluate the effectiveness and cost-effectiveness of modified Pilates exercises compared to aerobic exercises in the treatment of patients with fibromyalgia.

## Methods

### Study design

This study is a randomized controlled trial with parallel group and blinded assessor.

### Study settings

Participants will be treated at the Center for Excellence in Clinical Research in Physical Therapy at Universidade Cidade de São Paulo in Sao Paulo, SP, Brazil. This project was approved by the Research Ethics Committee of Universidade Cidade de São Paulo (CAAE: 51328215.1.0000.0064). It was also prospectively registered on Clinical Trials Registry (NCT03050606) and received funding from the Sao Paulo Research Foundation - FAPESP (process number 2016/12962–0 and 2015/21590–6). If there is a need to change the protocol, the changes will be immediately reported to the Research Ethics Committee and carried out at the registration site before the first patient is admitted to the study. The flow of participants through the study will follow the recommendations of the Consolidated Standards of Reporting Trials Statement and is outlined in Fig. 1.

**Fig. 1 Fig1:**
[figure not shown]
Study design

### Sample size calculation

The study was designed to detect a clinically significant 8 points (14%) difference in the impact of fibromyalgia assessed by the Fibromyalgia Impact Questionnaire eight weeks after randomization (estimated standard deviation = 12), assuming α = 0.05, statistical power of 80%, and loss to follow-up of 15%. This value represents the minimal clinically important difference [26]. The sample size calculation resulted in a sample of 98 participants divided into two groups of 49 each. To reach this number, the study will be promoted in community newspapers and on the internet.

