### Assessment of clinical outcomes

Before baseline assessment, the participants will give consent and sign the Informed Consent Form. A blinded assessor will confirm the eligibility criteria and the diagnosis of fibromyalgia through the criteria of the American College of Rheumatology 2010 [2]. Next, demographic and anthropometric data will be collected, as well as information on the use of medications (type and quantity) for fibromyalgia and physical therapy or other previous treatment. Finally, the participants will be assessed for the primary and secondary outcomes. The assessments will be performed at baseline, eight weeks, six months, and 12 months after randomization, and in the last three assessments, the patients will be instructed not to provide information about their treatment to the blinded assessor. In the follow-ups assessments, patients will also be asked about the use of medication and physical activity or other treatment for fibromyalgia. The baseline and eight-week assessments will be face-to-face, and the six- and twelve-month assessments will be conducted over the phone to minimize loss to follow-up. In the eight-week assessment patients will also be asked about their satisfaction with the treatment. All of the scales and the questionnaire used in this study have already been translated and adapted to Brazilian Portuguese [29–41].

The primary outcome is the impact of fibromyalgia eight weeks after randomization. The secondary outcomes are: impact of fibromyalgia six and 12 months after randomization; pain intensity, kinesiophobia, sleep quality, health-related quality of life and specific disability eight weeks, six months, and 12 months after randomization; pain intensity at each session, before and after treatment; and functional capacity eight weeks after randomization (Table 1).

**Table 1 Tab1:** Description of the outcome measures

Measure	Construct	Description

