Fibromyalgia Impact Questionnaire (FIQ) [30]	Fibromyalgia impact	10-item questionnaire. Item 1 contains 10 questions related to functionality, rated on a 4-point Likert scale ranging from 0 (always) to 3 (never). In items 2 and 3, the participants mark the number of days that they felt well and the number of days they were unable to work due to fibromyalgia in the last seven days. Items 4 to 10 are composed of numerical scales that rate work difficulty, pain, fatigue, morning tiredness, stiffness, anxiety, and depression. The FIQ score ranges from 0 to 100 points and higher values ​​indicate a greater impact of fibromyalgia on quality of life. In general, the scores of patients with fibromyalgia have an average of 50 points, but in those patients with severe impairment, values ​​exceed 70 points.
Pain Numerical Rating Scale (PNRS) [29]	Pain intensity	11-point numerical scale (0 to 10) that ranges from 0 (no pain) to 10 (pain as bad as it could be). In the baseline and follow-up assessments, the participants will rank their average pain in the last seven days. In assessing pain at each session, the participants will rate their pain before and after treatment.
Tampa Scale of Kinesiophobia (TSK) [31, 32]	Kinesiophobia	17-item questionnaire that addresses the fear that physical activity will cause pain or recurrence of the injury, with answers ranging from 1 (strongly disagree) to 4 points (strongly agree). For the final score, it is necessary to reverse the scores of questions 4, 8, 12, and 16. The total score varies between 17 and 68 points, and the higher the score is, the greater the degree of kinesiophobia.
Patient-Specific Functional Scale (PSFS) [29]	Specific disability	Scale in which participants will identify the three main activities that they feel incapable of doing or have difficulty doing because of fibromyalgia. Next, the participants will rate how able they feel capable of performing the activities identified on an 11-point scale, ranging from 0 (unable to perform activity) to 10 (able to perform the activity at preinjury level). The average of the three activities will be calculated, and the higher the score is, the greater the specific capacity of the patient.

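### The stated inputs give 84 to 88 participants, not 98, so at least one input or adjustment behind the sample size is unreported

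*Protocol article*

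**What the plan says.** The Sample size calculation section of the protocol article says the trial was "designed to detect a clinically significant 8 points (14%) difference in the impact of fibromyalgia", measured eight weeks after randomisation, with "estimated standard deviation = 12" and "assuming α = 0.05, statistical power of 80%, and loss to follow-up of 15" per cent. It identifies the target with the minimal clinically important difference, citing an outside source. It then gives the result: "The sample size calculation resulted in a sample of 98 participants divided into two groups of 49 each".

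The endpoint matches the one named under Assessment of clinical outcomes: "The primary outcome is the impact of fibromyalgia eight weeks after randomization".

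The section names no formula or test and does not say whether alpha is one- or two-sided. It mentions no further allowance, such as a non-parametric correction, a multiplicity adjustment or rounding up. The Statistical analysis section plans linear mixed models for all outcomes.

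Table 1, under Assessment of clinical outcomes, describes the questionnaire as running from 0 to 100 and says that, in general, "the scores of patients with fibromyalgia have an average of 50 points".

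**The concern.** A sample size paragraph that prints every input and the answer should be reproducible by hand. This one is not: the answer is more than 10% above what the inputs give, too much for rounding. Readers will use these numbers to judge a null or borderline primary result, because they say what difference the trial could have detected and with what probability. If they do not fit together, the reader cannot tell which design was actually specified.

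This is not a detail that an article leaves to a fuller protocol or analysis plan. Both the inputs and the result are printed, and they disagree.

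A smaller matter sits in the same sentence. The target is given both as 8 points and as 14%, with no statement of what the percentage is taken from.

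**Working it through.** **Inputs**, all from the Sample size calculation section: difference 8, SD 12, alpha 0.05, power 80%, loss 15%, two equal groups. Two-sided testing is my assumption, since sidedness is not stated.

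**Step 1: evaluable participants per group.**

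- Normal approximation: n = 2 × (1.960 + 0.8416)² × 12² / 8² = 35.3, so 36.
- Two-sample t test (noncentral t): 36.3, so 37.

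**Step 2: allowance for 15% loss.** Both common conventions are shown. Dividing by 0.85 is the correct one; multiplying by 1.15 is a frequent shortcut.

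| Evaluable per group | ÷ 0.85 | Total | × 1.15 | Total |
|---|---|---|---|---|
| 36 (normal) | 42.4, so 43 | 86 | 41.4, so 42 | 84 |
| 37 (t test) | 43.5, so 44 | 88 | 42.6, so 43 | 86 |

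The range is 84 to 88. The stated 98 exceeds it by 98 − 88 = 10 to 98 − 84 = 14 participants, or 10/88 = 11% to 14/84 = 17%. One-sided alpha moves further away: 28 evaluable per group by the normal formula, 33 after loss, 66 in total.

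**Step 3: power that 98 actually gives on the stated inputs.** With 49 per group and 15% lost, 49 × 0.85 = 41.65 remain.

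- 41 per group: 84.7% (t test).
- 42 per group: 85.5% (t test).
- No loss, 49 per group: 90.4% (t test).

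The t test needs 37 evaluable per group for 80% power, so on the stated difference and SD the trial would keep 80% power with up to 12 of 49 lost per group (24.5%).

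**Step 4: what would give 49 per group.** One item is changed at a time, using the t test and division by 0.85 unless noted.

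- Power 84%: 41 evaluable, 41/0.85 = 48.2, so 49. At 85% power, 49 arises from the normal formula (41 evaluable), or from the t test with multiplication (42 × 1.15 = 48.3).
- SD 12.7: 41 evaluable, so 49.
- Difference 7.6: 41 evaluable, so 49.
- Loss of about 24.5%: 37/0.755 = 49.0.
- The 15% increase applied twice: 37 × 1.15 × 1.15 = 48.9, so 49.
- 90% power with no loss allowance: 49.
- A flat 15% increase for a rank test: 36.3 × 1.15 = 41.8, so 42; then 42 × 1.15 = 48.3, so 49 (or 42/0.85 = 49.4, so 50).

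Several unrelated routes reach the printed figure, and some leave power, SD and difference exactly as stated. The result alone cannot identify the cause.

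**Step 5: the percentage.** 8/0.14 = 57.1, so 8 points is 14% of a reference value of about 57. It is 8% of the full 0 to 100 range. Against the general average of 50 in Table 1, 14% would be 7 points.

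**The case against.** The strongest reply is that nothing harmful follows. The printed total is larger than needed, the stated 80% power is met and exceeded, and the endpoint, analysis and enrolment are unaffected. The total may include an allowance that was simply not written down. All of this stands, and it makes the point minor. It does not make the paragraph correct: the article says the calculation with these inputs resulted in 98, and it does not. Nothing stated supplies the missing allowance, and a planned linear mixed model gives no ground for assuming a rank-test correction.

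A reader might go further and infer that the power, the SD or the target difference must be the misreported item. The document does not support that. A loss allowance near 24.5%, or the 15% increase applied twice, gives 49 per group with those three unchanged. The values in Step 4 are possibilities, not estimates of what was entered.

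A reader might also combine the 14% with the average of 50, conclude that the real target is 7 points, and find the trial underpowered (75.2% with 42 per group). That does not hold either. The target is stated in points, as 8. The 50 is a general description of patients with fibromyalgia, not this trial's assumed baseline, and the trial requires a pain score of at least 3 at entry. A reference mean of about 57 would reconcile the two figures. The percentage has an undefined denominator; no contradiction is shown.

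**Conclusion.** The paragraph is wrong as written, at minor severity. The stated inputs give 36 to 37 evaluable and 42 to 44 randomised per group, 84 to 88 in total, against the stated 49 and 98. At least one input or adjustment used (power, SD, difference, loss allowance or an unstated correction) is not the one reported, and the document does not show which.

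If the printed inputs are the true ones, the discrepancy is in the safe direction: about 85% power after 15% loss instead of 80%. No shortfall in power is shown.

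This rests on a two-sided test of two independent means with equal groups, the ordinary reading of the section. Neither the normal nor the t version, with either loss convention, comes within 10 participants of 98, and a one-sided test is further off.

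**What to change.** Keep 98 and make the paragraph consistent in one of two ways:

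- Restate the power: with 98 randomised and 15% loss (about 42 evaluable per group), power is about 85% to detect 8 points at SD 12 with two-sided alpha 0.05.
- Or report what was actually entered: formula or software routine, sidedness, how loss was added, and the difference, SD, power and loss rate that yield 49 per group.

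Only the investigators can say which applies; the second is preferable if the original calculation can be recovered. In the same edit, state which reference value the 14% is taken from, or delete it so that the 8-point target stands alone.

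The cost is one paragraph of wording. No participants, procedures or analyses change.

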### Eligibility criteria

The study will include patients of both genders who meet the fibromyalgia classification criteria of the American College of Rheumatology 2010 [2], aged between 20 and 75 years, and with pain intensity greater than or equal to 3 points in the Pain Numerical Rating Scale [27]. The exclusion criteria will be contraindications to physical exercise [28], pregnancy, uncontrolled systemic diseases (diabetes mellitus, systemic arterial hypertension, and thyroid dysfunctions), neurological, cardiorespiratory, and musculoskeletal conditions that interfere in the treatment, e.g., paralysis, significant loss of sensitivity (such as diabetic foot), changes in level of consciousness and understanding, advanced joint diseases, injury or severe pain in the lower limbs that limit the performance of aerobic exercises (such as severe arthrosis, hip or knee arthroplasty, severe rheumatoid arthritis, cervicalgia with irradiation to the upper limbs, meniscus injury, plantar fasciitis, partial or total muscle tears, amputations, among others), recent surgery, and inability to understand or speak Portuguese. Prior screening will be conducted by telephone by a previously trained student, with exception of irradiated pain, which will be assessed in a face-to-face assessment. Participants will be asked to not look for other treatment (whether based on exercises or non-pharmacological interventions) while undertaking the study intervention.

### Assessment of clinical outcomes

Before baseline assessment, the participants will give consent and sign the Informed Consent Form. A blinded assessor will confirm the eligibility criteria and the diagnosis of fibromyalgia through the criteria of the American College of Rheumatology 2010 [2]. Next, demographic and anthropometric data will be collected, as well as information on the use of medications (type and quantity) for fibromyalgia and physical therapy or other previous treatment. Finally, the participants will be assessed for the primary and secondary outcomes. The assessments will be performed at baseline, eight weeks, six months, and 12 months after randomization, and in the last three assessments, the patients will be instructed not to provide information about their treatment to the blinded assessor. In the follow-ups assessments, patients will also be asked about the use of medication and physical activity or other treatment for fibromyalgia. The baseline and eight-week assessments will be face-to-face, and the six- and twelve-month assessments will be conducted over the phone to minimize loss to follow-up. In the eight-week assessment patients will also be asked about their satisfaction with the treatment. All of the scales and the questionnaire used in this study have already been translated and adapted to Brazilian Portuguese [29–41].

The primary outcome is the impact of fibromyalgia eight weeks after randomization. The secondary outcomes are: impact of fibromyalgia six and 12 months after randomization; pain intensity, kinesiophobia, sleep quality, health-related quality of life and specific disability eight weeks, six months, and 12 months after randomization; pain intensity at each session, before and after treatment; and functional capacity eight weeks after randomization (Table 1).

**Table 1 Tab1:** Description of the outcome measures

Measure	Construct	Description
Fibromyalgia Impact Questionnaire (FIQ) [30]	Fibromyalgia impact	10-item questionnaire. Item 1 contains 10 questions related to functionality, rated on a 4-point Likert scale ranging from 0 (always) to 3 (never). In items 2 and 3, the participants mark the number of days that they felt well and the number of days they were unable to work due to fibromyalgia in the last seven days. Items 4 to 10 are composed of numerical scales that rate work difficulty, pain, fatigue, morning tiredness, stiffness, anxiety, and depression. The FIQ score ranges from 0 to 100 points and higher values ​​indicate a greater impact of fibromyalgia on quality of life. In general, the scores of patients with fibromyalgia have an average of 50 points, but in those patients with severe impairment, values ​​exceed 70 points.
Pain Numerical Rating Scale (PNRS) [29]	Pain intensity	11-point numerical scale (0 to 10) that ranges from 0 (no pain) to 10 (pain as bad as it could be). In the baseline and follow-up assessments, the participants will rank their average pain in the last seven days. In assessing pain at each session, the participants will rate their pain before and after treatment.
Tampa Scale of Kinesiophobia (TSK) [31, 32]	Kinesiophobia	17-item questionnaire that addresses the fear that physical activity will cause pain or recurrence of the injury, with answers ranging from 1 (strongly disagree) to 4 points (strongly agree). For the final score, it is necessary to reverse the scores of questions 4, 8, 12, and 16. The total score varies between 17 and 68 points, and the higher the score is, the greater the degree of kinesiophobia.
Patient-Specific Functional Scale (PSFS) [29]	Specific disability	Scale in which participants will identify the three main activities that they feel incapable of doing or have difficulty doing because of fibromyalgia. Next, the participants will rate how able they feel capable of performing the activities identified on an 11-point scale, ranging from 0 (unable to perform activity) to 10 (able to perform the activity at preinjury level). The average of the three activities will be calculated, and the higher the score is, the greater the specific capacity of the patient.
Euroqol 5 dimensions (EQ-5D-3L) [41]	Health-related quality of life	Two-part questionnaire: the first part records the severity of the problem in each of the five dimensions of the questionnaire, and the second part contains a 20-cm vertical visual analogue scale ranging from 0 to 100, where 0 corresponds to the worst imaginable health states and 100 corresponds to the best imaginable health states. Its five dimensions are mobility, self-care, usual activities, pain/discomfort, and anxiety/depression, and each dimension has three levels of severity (no problems, moderate problems, and extreme problems). Health status is labeled with a five-digit number that represents the severity level in each dimension. For example, 11111 represents no problem in any dimension, whereas 33333 represents extreme problems in all five dimensions.
Short-Form 6 dimensions (SF-6D) [33, 34, 39, 40]	Health-related quality of life	Questionnaire with six domains: physical functioning, role limitations, social functioning, pain, mental health, and vitality. The SF-6D score represents the strength of a patient’s preference for a particular health condition and ranges from zero (worst health state) to one (best health state).
Pittsburgh Sleep Quality Index (PSQI) [38]	Sleep quality	Questionnaire composed of 19 self-report questions and five questions that must be answered by a roommate or bed partner (which will not be used in this assessment). The 19 questions are classified into seven components (subjective sleep quality, sleep latency, sleep duration, habitual sleep efficiency, sleep disturbances, use of sleeping medication, and daytime dysfunction), which are classified into a score ranging from 0 (none in the last month) to 3 (three or more times/week). The sum of the scores for these seven components ranges from 0 to 21, where higher scores indicate poorer sleep quality. An overall score greater than 5 indicates great difficulty in at least two components, or moderate difficulty in more than three components.
Six-minute Walk Test (6MWT) [35–37]	Functional capacity	Before the test, the patient should rest for at least 10 min. The test will be performed on a flat, firm surface that is 30 m in length and seldom traveled. Two cones will be used to mark the starting point and the 30-m point where the participant must turn around and continue walking without hesitation. The surface will also have markings every 3 m with adhesive tape. The participants must walk for 6 min as fast as they can, without running, while the assessor times the walk (for 6 min) and counts how many laps are completed (each lap is 60 m). The participants will be allowed to slow down and/or stop during the test (including leaning against the wall) if necessary, but will be advised to walk again as soon as possible. Every minute of the test, the assessor will say the following words of encouragement: “You are doing well. You have x minutes to go”. With 15 s left to complete the test, the assessor will say: “In a moment I’m going to tell you to stop. When I do, just stop right where you are and I will come to you”. When the stopwatch is stopped, the assessor will say the word “stop”, go to the participant, and mark the point where he stopped with tape. After the test, the assessor will ask the patient to complete Borg scale. The distance traveled will be calculated by adding the number of laps to the meters walked until the participant stops.

